#### Data Collection

Data will be collected by administering questionnaires to the identified respondents in the sampled compounds within the communities. The survey questionnaires will be administered by a trained research team. All surveys will be administered using SurveyCTO, an electronic data collection platform for smartphones, and data will be uploaded to a remote server after each day of data collection. Interviews will be conducted in local languages using the questionnaires provided by the Malaria Consortium, with data collectors translating from the Portuguese questionnaire on the spot and assigning responses to predefined answer categories in SurveyCTO. For the age eligibility indicator, survey respondents may be asked to present a birth certificate or vaccination card to the data collector to verify the child’s date of birth. The duration of data collection is expected to last for 7 days during the first week of March 2021. 

#### Data Analysis

Data analysis will be carried out using Stata 16. Coverage will be calculated using the proportion command. Population size weights will be applied using the svy command as appropriate for estimates of coverage indicators when it is not possible to achieve a self-weighting sample. All indicators of interest will be calculated as proportions by district and an average across both districts.

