#### Study Design

For this objective, the design will be a cross-sectional cluster randomized survey to evaluate the coverage level and quality of SMC piloted in the Malema and Mecuburi districts. Households refusing to participate in the study will be replaced with the next eligible household until the estimated sample size is attained.

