#### Sample Size and Technique

The end-of-round survey will use multistage random samples of households in areas covered by the Malaria Consortium’s SMC pilot and will intend to achieve a representative sample of the target population at the district level to estimate the coverage of SMC at the level of individual eligible children. The sampling protocol aims to achieve a self-weighted sample with sampling units selected with a probability proportional to size. Only at the last stage of sampling (ie, at the household level) will a constant number of eligible children (1 child per household) be selected. The survey will be powered to provide an estimate of SMC coverage for children aged 3-59 months with a margin of error of 5%, while also providing a representative sample of children aged 60-119 months. The main sampling frame for the selection process will be a list of villages. Villages will then be randomly selected using the probability proportional to size. Villages will be the primary unit of sampling through which households and eligible children will be selected randomly. This may be reviewed once the study starts if this approach is not feasible in practice. A primary caregiver in this survey refers to any individual, aged at least 18 years, with the primary responsibility of feeding and daily care of at least one child aged less than 5 years, in a household where he or she has been a resident before the start of the SMC pilot or 1 month before the last cycle of SMC. The sample size calculation was performed using Stata 16 using the *svysampsi* command, based on the following assumptions: (1) the assumed intracluster correlation is 0.2; (2) 15 eligible children per cluster (b=cluster size); (3) the (design/cluster effect) = 1 + (b − 1) intracluster correlation = 1 + (15 − 1) 0.2 = 3.8; (4) the coverage rate of SMC in children aged 0-4 years of at least 80% (and in children aged 5-9 years of at most 20%); (5) a margin of error of 5%; (6) finite population adjustment is applied (75,000); (7) nonresponse rate of 5%; and (8) assumed ratio of children aged 5-9 years to those aged 0-4 years of 0.88.

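### The coverage survey's analysis rule calls for survey methods only when weights are needed, not because villages are clusters; followed as written in the intended self-weighted case, it would give intervals that are too narrow

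*Protocol article*

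**What the plan says.** All of this is in the protocol article under Coverage and Quality Evaluation (End-of-Round Survey).

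- **Study Design:** "the design will be a cross-sectional cluster randomized survey to evaluate the coverage level and quality of SMC".
- **Sample Size and Technique:** villages are the primary sampling unit. On weighting, "The sampling protocol aims to achieve a self-weighted sample with sampling units selected with a probability proportional to size". The precision target is a 5-point margin of error for children aged 3-59 months. The sizing assumptions include "the assumed intracluster correlation is 0.2" and 15 children per cluster, which the plan turns into a design effect of 3.8.
- **Sampling Procedure:** 1842 children are required. The plan settles on 120 clusters of 15, which is 1800 children, with 60 clusters in each district.
- **Data Analysis:** "Coverage will be calculated using the proportion command. Population size weights will be applied using the svy command as appropriate". The condition attached to the second sentence is "when it is not possible to achieve a self-weighting sample". Results are to be given as follows: "All indicators of interest will be calculated as proportions by district and an average across both districts".

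The Data Analysis paragraph names no standard error, no interval method and no primary sampling unit.

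**The concern.** Two separate features of a survey design call for survey commands. Unequal selection probabilities call for weights, which affect the point estimate. Cluster sampling calls for a variance that allows children in the same village to resemble each other. The plan makes the use of `svy` depend on the first feature only.

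The condition matters because a self-weighted sample is what the sampling aims for, so the situation in which the rule does not call for `svy` is the intended one. The split between districts would hardly trigger weighting either: the target populations in Table 1 are nearly equal (36,469 and 35,474) and each district gets 60 clusters. Run on its own, without the `svy` prefix or a cluster variance option, `proportion` treats the children as independent.

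What is at stake is the stated precision. Coverage and quality belong to one of the study's two primary aims, and the survey was sized to a precision target. An interval that omits clustering would make that target look more comfortably met than it is.

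**Working it through.** **Inputs from the plan.** Coverage p = 0.80; margin d = 0.05; ICC = 0.2; cluster size b = 15; finite population 75,000; nonresponse 5%; ratio of older to younger children 0.88; 120 clusters, 1800 children, 60 clusters per district. The 95% level (z = 1.96) is an assumption, since the article does not state it.

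**Step 1: reproduce the plan's sample size.**
- Simple random sample: 1.96² × 0.8 × 0.2 / 0.05² = 245.9.
- Finite population correction: 245.9 / (1 + 244.9/75,000) = 245.05.
- Design effect: 1 + (15 − 1) × 0.2 = 3.8; 245.05 × 3.8 = 931.2.
- Nonresponse: 931.2 / 0.95 = 980.2.
- Both age groups: 980.2 × 1.88 = 1842.8, against 1842 stated.

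Without the design effect the same chain gives 245.05 / 0.95 × 1.88 = about 485. Clustering therefore accounts for a nearly fourfold increase in the sample.

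**Step 2: children aged 3-59 months who enter the coverage estimate.** If the 15 children per cluster span 3-119 months in the assumed ratio:
- Overall: 1800 / 1.88 = 957. Per district: 900 / 1.88 = 479. Per cluster: 15 / 1.88 = about 8.
- Design effect: 1 + (7.98 − 1) × 0.2 = 2.40.

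**Step 3: half-widths at p = 0.80.** The independent-children half-width is 1.96 × √(0.16/n). The cluster-adjusted half-width multiplies this by √(design effect). A nominal 95% interval that omits clustering covers 2Φ(1.96/√(design effect)) − 1. The finite population correction is negligible at these sizes and is left out.

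| Children in the estimate | n | Design effect | Independent | Cluster-adjusted | Ratio | Coverage |
|---|---|---|---|---|---|---|
| 3-59 months, both districts | 957 | 2.40 | ±2.5 | ±3.9 | 0.65 | 79% |
| 3-59 months, one district | 479 | 2.40 | ±3.6 | ±5.5 | 0.65 | 79% |
| All 15 per cluster, both districts | 1800 | 3.8 | ±1.8 | ±3.6 | 0.51 | 69% |
| All 15 per cluster, one district | 900 | 3.8 | ±2.6 | ±5.1 | 0.51 | 69% |

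**Step 4: sensitivity to the ICC.** The ICC of 0.2 is a planning value. Smaller values, taken here as assumptions, shrink the problem without removing it:
- About 8 children per cluster: ratio 0.77 and coverage 87% at ICC 0.10; ratio 0.86 and coverage 91% at ICC 0.05.
- All 15 per cluster: ratio 0.65 at ICC 0.10 and 0.77 at ICC 0.05.

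**The case against.** The strongest defence is that the paragraph describes how coverage is calculated, which is a point estimate, and says nothing about intervals. `proportion` can be run under `svy` or with a cluster-robust variance, so naming it does not commit anyone to the wrong standard error. The authors clearly know that the survey is clustered, because their sample size depends on it. A condensed article may leave variance syntax to a fuller document.

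Most of this stands, and it limits what can be claimed. A reader might infer that clustering is ignored as a matter of plan. The article does not say so; it is silent on intervals, and an analyst could still declare the village.

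A reader might also infer that intervals will be about half the proper width throughout. That needs ICC 0.2 and all 15 children per cluster in the estimate. Combining 957 children aged 3-59 months with the design effect of 3.8 would give ±4.9 points. The plan's sizing makes the same pairing, but it does not fit about 8 such children in each of 120 clusters. The ICC was also assumed for the coverage sample size, so its value for the quality indicators is unknown.

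Finally, a reader might expect spurious differences between districts or monthly cycles. No such tests are planned; the indicators are descriptive.

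What the defence does not remove is that the article goes beyond silence. It states when `svy` is to be used, and the condition is the wrong one. Clustering is present whether or not the sample turns out self-weighted.

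**Conclusion.** The point holds as a wrongly conditioned rule with a conditional consequence. If the rule is followed literally in the self-weighted case, intervals for children aged 3-59 months would be about 0.65 of the proper width, falling to about 0.51 if all 15 children per cluster contribute. These figures rest on the planning ICC of 0.2, 80% coverage, a 95% level and, for the first, the assumed age ratio of 0.88.

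The practical effect is clearest by district, which is a planned reporting level. A stated ±3.6 would sit inside 5 points where the cluster-adjusted ±5.5 would not, although the article does not say that the 5-point margin applies to each district. Overall, both ±2.5 and ±3.9 are within it.

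Point estimates are sound under self-weighting, and the survey is descriptive. Severity is moderate.

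**What to change.** Separate the two reasons for using survey methods and make the design declaration unconditional:

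- `svyset` the data with village as primary sampling unit and district as stratum in every case, with weights of 1 if the sample is self-weighting and population size weights if it is not.
- Compute all coverage and quality indicators, and their intervals, with `svy: proportion`, by district and overall.
- Report the realised design effect, so that readers can compare it with the planned 3.8.

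This takes a sentence in the plan and a line or so of Stata, with no new data. The only downside is that the stated intervals become wider, by a factor of about 1.55 (√2.40) for children aged 3-59 months at the planning ICC.

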### Availability of Data and Materials

The associated study protocol and data collection tools will be made available upon request from the corresponding author. Quantitative data sets will be available from the corresponding author upon reasonable request after the completion of primary analyses and dissemination of results. Qualitative study data sets will not be available, as they may include identifiable information that could compromise participant identity.

## Results

Data collection and analysis from all six objectives will be completed by September 2021.

## Discussion

### Principal Findings

This study will provide a unique contribution to the evidence on the prevalence of SPAQ resistance in Mozambique and more broadly in the region, and to what extent it may challenge the protection that SMC confers. Furthermore, this first evaluation of SMC implementation in this context will generate insights on the enablers, challenges, perceptions, feasibility, acceptability, quality, and coverage of this intervention in situ. This study is vital, as it is the first time that SMC is implemented in East and Southern Africa.

Recent evidence from the ACCESS-SMC program showed that the protective effectiveness of each monthly treatment was similar to that observed in randomized controlled trials [44,45]. In 2 countries with district health information software-2 databases established before SMC scale-up (ie, The Gambia and Burkina Faso), estimated reductions of 57% and 42% in the number of malaria deaths in district hospitals were determined for the SMC intervention period, and reductions of 53% and 45% in the number of outpatient cases, respectively [8]. Similar reductions were observed in the number of outpatient malaria cases in other countries [8]. These results represent the first large-scale evaluation of SMC implemented by national programs and provide the first evidence of an impact on malaria deaths. Earlier studies in Burkina Faso and Mali showed effects on prevalence [46,47] and cost-saving benefits [9,48].

Molecular markers of SPAQ resistance occurred at a low prevalence in previous studies in the Sahel, consistent with the effectiveness of SMC observed in several case-control studies. However, there is evidence of selection for resistance to SP in parasites sampled from the same age group in the areas where SMC will be implemented for the first time in Mozambique. Therefore, resistance to both SPAQ needs to be monitored via standardized methods, across all regions in Mozambique where SMC is used, to provide early warning of loss of effectiveness.

### Limitations

Leakage of SPAQ to older age groups not targeted by SMC programs raises a concern for the development of drug resistance, as doses administered are unlikely to offer sufficient protection against malaria transmission. This also influences the secondary data analysis in the same way; leakage reduces the apparent effect size in the targeted age group.

### Conclusions

This research will be a novel contribution to our understanding of whether SPAQ, when used for SMC, can confer a protective effect against malaria in children aged 3-59 months in a region where malaria transmission is seasonal and SP resistance is expected to be high. In addition, the findings from this study will inform future SMC implementation in Mozambique and other countries and potentially enhance the quality of SMC distribution in terms of quality, coverage, and acceptability. Subsequent phases are expected to provide a more comprehensive assessment of the effectiveness and sustainability of SMCs.

## Abbreviations

ACCESS-SMC: Achieving Catalytic Expansion of SMC in the Sahel
AQ: amodiaquine
dhfr: dihydrofolate reductase
dhps: dihydropteroate synthetase
FGD: focus group discussion
pfcrt: Plasmodium falciparum chloroquine resistance transporter gene
pfmdr1: Plasmodium falciparum multidrug resistance gene 1
RDT: rapid diagnostic test
SMC: seasonal malaria chemoprevention
SP: sulfadoxine-pyrimethamine
SPAQ: sulfadoxine-pyrimethamine and amodiaquine
WHO: World Health Organization
